#### Hyperinsulinemic euglycemic clamp

On the morning of the test day, subjects will report to the university in the fasted state (fasted since 8PM the day before). A teflon cannula will be inserted into an antecubital vein and will be used for the infusion of glucose tracer, glucose, insulin, lipid/saline and carnitine/saline. A 'manifold' will be attached to the cannula (see figure 6a below). Separate infusion lines will be connected to this manifold for the infusion of the glucose tracer, glucose, insulin, lipid/saline and carnitine/saline. Blood will be sampled from a second cannula, inserted into a superficial dorsal hand vein. This venous blood will be arterialized by placing the hand into a hot-box, which blows warm air (~65 °C). After taking a fasting blood sample (7mL), a primed (2.4 mg/kg) constant infusion (0.04 ml/kg/min) of the glucose tracer ([6,6-D2]glucose) is initiated (t=0). This is a naturally occurring isotope, which is in no way harmful to humans and will be obtained from Cambridge Isotope Laboratories, inc. (Andover, MA, USA). Subsequently, a percutaneous muscle biopsy of the vastus lateralis muscle will be taken (see appendix K6 for the SOP muscle biopsy). After 90 minutes infusion of 6,6-D2 glucose, to allow isotopic equilibration, four additional blood samples will be drawn (7ml for each blood sample at t=90, 100, 110 and 120). In addition, during the last 30 minutes of this basal period (t=90-120), substrate oxidation is measured with indirect calorimetry (ventilated hood).

[figure not shown]

**Figure 6A: Manifold for the connection of the separate infusion lines**

Insulin sensitivity will be measured by performing simultaneously a 6-hour hyperinsulinemic euglycemic clamp, using the technique of DeFronzo et al. [15]. At t=120, insulin infusion (Novorapid, Novo Nordisk) will be started at a fixed rate (40 mU/m^2/min) from 0 to 6 hours (t=120 until t=480). At the same time a variable co-infusion of 20% glucose will be started. At regular time points (every 5 to 10 minutes), a small volume of blood (1.0mL) will be sampled for immediate determination of plasma glucose concentration. When necessary, glucose infusion rate will be adjusted to obtain plasma glucose levels of ~5 mmol/L (euglycemia). After 330 minutes infusion of insulin, four additional blood samples will be drawn (7ml for

each blood sample at  $t=450$ ,  $460$ ,  $470$  and  $480$ ). In addition, during the last 30 minutes of this hyperinsulinemic period ( $t=450-480$ ), substrate oxidation is measured with indirect calorimetry (ventilated hood). Hereafter, whole body insulin sensitivity can be expressed as the rate of glucose appearance (Ra) and disappearance (Rd).

In two intervention arms (LIPID+PLAC and LIPID+CAR), a lipid emulsion (Intralipid 20%, Fresenius-Kabi) will be administered. This emulsion is based on long-chain fatty acids (10% safflower and 10% soybean oil) and will be administered at a rate of 90ml/h for 6 hours (starting at  $t=0$ ). In the control trial, saline will be infused. In the LIPID+CAR condition intravenous L-carnitine infusion will take place. At the onset of L-carnitine infusion ( $t=0$ ) a bolus dose of 4 mg/kg will be administered over 10 min to rapidly reach a supraphysiological plasma concentration of approximately 200  $\mu\text{mol/liter}$ . This will be followed by a constant infusion at 4 mg/kg/h for the remaining of the clamp. In the non-carnitine conditions saline will be infused matching for the total volume infused with carnitine infusion.

Additional blood samples (7mL) will be drawn at  $t=180$ ,  $t=240$ ,  $t=300$ ,  $t=360$  and  $t=420$  for determination of glucose, FFA, insulin and triglycerides. Between  $t=240$  and  $t=270$  an additional ventilated hood measurement will be performed to assess substrate oxidation. At  $t=480$  a muscle biopsy will be taken in all three intervention arms (LIPID+CAR / LIPID+PLAC / SALINE+PLAC). Thereafter insulin 6,6-D2 glucose, lipid/saline and carnitine/saline infusion will be stopped, while glucose infusion will be continued to prevent hypoglycemia, and subjects will be offered a lunch. An overview of the blood draws taken during the clamp is provided in appendix 2A. An overview of the total amount of blood taken during the entire study is calculated in appendix 2B.

[figure not shown]

Figure 6b: overview hyperinsulinemic euglycemic clamp

De SOP hyperinsulinemic euglycemic clamp is added in appendix K6. The time of insulin administration (6 hours) deviates from the SOP (2.5 hours) due to the additional infusion of Intralipid in this study. Lipid infusion during a clamp is often performed in the metabolic field and also several times before in our research group via the design explained above. As a result of the additional lipid infusion it does not take 2.5 hours to achieve stable glucose values but 6 hours. These six hours are necessary because it takes 3 to 4 hours until insulin resistance occurs regarding glucose infusion rates. The SOP is followed on all the other aspects.

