### 3. STUDY DESIGN

In this study we will investigate whole body insulin sensitivity of healthy adults during a 6-hour hyperinsulinemic euglycemic clamp in a placebo controlled randomized cross over design. All subjects will undergo three hyperinsulinemic euglycemic clamps. Two hyperinsulinemic euglycemic clamps will be performed with simultaneous infusion of lipids. In one of these lipid infusion trials, subjects will simultaneously receive L-carnitine infusion (=LIPID + CAR). In the other trial, L-carnitine infusion will be replaced by placebo infusion in the form of saline (=LIPID + PLAC). In a third hyperinsulinemic euglycemic clamp, lipid infusion will be replaced by the infusion of saline and will serve as a control for the lipid infusion (=SALINE + PLAC). All three trials will be separated by at least two weeks. Subjects will be blinded, so no information about the infused substances will be provided to them.

[figure not shown]

**Inclusion:** Subjects will be recruited in and near the vicinity of Maastricht by means of posters and advertisements in local newspapers. When subjects react on the advertisement, they will be contacted by telephone. During this telephonic interview the study protocol will be verbally explained to the subject and some of the basic inclusion criteria will be checked, such as weight, height, BMI, age, sports participation, general health, dietary habits, MRI contra-indications and being vegetarian. When this is in compliance with our study protocol, subjects will receive the detailed subject information via email or mail. They will be instructed to read it carefully, and to ask questions when things are unclear. Subjects get at least one week to carefully read all information provided to them. If they still want to participate after carefully reading the subject information and completely understand it, subjects will be invited to the university for signing the informed consent and to be screened subsequently.

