Previous studies investigating carnitine infusion during a hyperinsulinemic euglycemic clamp showed positive effects glucose infusion rate, glucose oxidation and non-oxidative glucose disposal after carnitine infusion compared to saline infusion [7, 17]. These studies infused a total amount of 1 gram carnitine over 3 hours. To achieve similar results in this study, we concluded that per three hours 1 gram of carnitine should be infused. During the current study, carnitine infusion will be six hours combined with lipids. This would result in a total carnitine infusion of approximately 2 grams due to the longer infusion time of carnitine. Natali et al. previously showed that a total amount of 2 grams of carnitine infused combined with lipid infusion results in positive effects on substrate oxidation [20]. Translating these previous studies into infusion rates and taking the maximal allowed doses of carnitine (30mg/kg/day) into account, we will use the following infusion rates. At the onset of L-carnitine infusion a bolus dose of 4mg/kg will be administrated over 10 minutes to rapidly reach a supraphysiological plasma concentration of approximately 200  $\mu\text{mol/L}$  of carnitine. This will be followed by a constant infusion of L-carnitine at 4 mg/kg/h (=0.07mg/kg/min) for the next 350 minutes to maintain hypercarnitinemia and to ensure that plasma carnitine concentration per se will not be rate limiting to muscle carnitine transport [6]. The total amount of intravenously infused L-carnitine will equal 28 mg/kg/day and therefore not exceed the maximal intravenous administration of 30mg/kg/day (Appendix D2).

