## 6.6 Dosages, dosage modifications and method of administration

L-Carnitine will be administrated intravenously as continuous infusion during the 6-hour hyperinsulinemic euglycemic clamp. The administration will start with a bolus of 4mg/kg for 10 minutes. A bolus will be administrated to ensure rapid supraphysiological plasma concentration of approximately 200µmol/L [6]. Subsequently, continuous L-carnitine infusion of 4mg/kg/h (=0.07mg/kg/min) will start for the remaining 350 minutes of the clamp in order to ensure that plasma carnitine concentrations per se will not be rate limiting to muscle carnitine transport [6]. The maximal administered dosage will be 28mg/kg and will not exceed the maximal daily allowed administration dosage of 30mg/kg per day (Appendix D2).

Intralipid will be administrated intravenously as continuous infusion during the 6-hour hyperinsulinemic euglycemic clamp at an infusion rate of 90ml/h. This lipid infusion during a clamp is a technique commonly used in human research to obtain insulin resistance and is commonly performed in our research group. This insulin resistance is defined as a 1.7-2 fold increase in free fatty concentrations. An infusion rate of 90ml/h has been shown previously to result in an almost 2-fold increase in free fatty acids [18,19].

The maximal administered dosage will be 540ml (108 grams of fat). The maximal allowed dosage equals 3 gram fat per kg body weight. For a individual of 70 kg this equals 210 grams of fat, much higher than the administration in this study.

Natriumchloride (0.9%) will be used as control condition for the Intralipid condition.

Natriumchloride (0.9%) will be administrated intravenously as continuous infusion during the 6-hour hyperinsulinemic euglycemic clamp at an infusion rate of 90ml/h to make sure the infused volumes in both conditions (LIPID and SALINE) are equal [18,19].

Natriumchloride 0.9% will also be used as control condition for the Carnitine infusion.

Natriumchloride 0.9% will be administrated intravenously as continuous infusion during the 6-hour hyperinsulinemic euglycemic clamp. The infusion volume of the natriumchloride will be equal to the infusion volume of carnitine. Since the infusion volume of carnitine is depended on weight this volume will differ per subject. For each individual subject the infusion volume of natriumchloride will be equal to the carnitine infusion volume in ml.

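### Section 8.3 starts lipid and carnitine at t=0 (tracer start) instead of t=120 (insulin start); followed literally, carnitine reaches 35.3 mg/kg against the protocol's own limit of 30 mg/kg/day

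*Protocol*

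**What the plan says.** Section 8.3 (Hyperinsulinemic euglycemic clamp) sets out the clamp-day timetable:

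- **Clock.** The tracer infusion "is initiated (t=0). This is a naturally occurring isotope". Basal blood samples and calorimetry follow at t=90-120.
- **Insulin.** It runs at a fixed rate "from 0 to 6 hours (t=120 until t=480"). The final samples and calorimetry are at t=450-480.
- **Lipid.** It "will be administered at a rate of 90ml/h for 6 hours", with the start given as t=0.
- **Carnitine.** A 4 mg/kg bolus over 10 minutes, also with t=0 as onset, is "followed by a constant infusion at 4 mg/kg/h for the remaining of the clamp".
- **Stop.** After the t=480 biopsy: "Thereafter insulin 6,6-D2 glucose, lipid/saline and carnitine/saline infusion will be stopped".

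Other sections describe infusions that coincide with the clamp:

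- Section 3: "Two hyperinsulinemic euglycemic clamps will be performed with simultaneous infusion of lipids".
- Section 5.1: "During the current study, carnitine infusion will be six hours combined with lipids".
- Section 6.6 places lipid and carnitine within the 6-hour clamp; after the bolus, the constant carnitine infusion "will start for the remaining 350 minutes of the clamp". The stated maxima are 28 mg/kg carnitine, under a limit of 30 mg/kg per day, and 540 ml (108 g) lipid, under a limit of 3 g fat per kg.
- Section 10.8 repeats these carnitine and lipid totals and limits, and section 12.1 repeats those for carnitine.

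**The concern.** On section 8.3's own clock, t=0 is two hours before the clamp begins. A start at t=0 and a stop after t=480 is an eight-hour infusion, which cannot be reconciled with the durations and totals elsewhere. For lipid the section also contradicts itself: six hours from t=0 ends at t=360, not t=480.

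Three things are at stake if staff work from the printed times:

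1. **Dose.** Carnitine would pass the daily limit that sections 5.1, 6.6, 10.8 and 12.1 say is respected.
2. **Baseline.** Metabolic flexibility is listed in section 8.1.1 among the main endpoints, as the change in RER from the basal to the insulin-stimulated state. With infusions from t=0, the basal RER would be measured under lipid in two arms and under lipid plus carnitine in one of them. The basal tracer samples would be affected too. So could the first biopsy, which follows the tracer start.
3. **Endpoint window.** If staff instead keep lipid to six hours from t=0, it is off before GIR, Rd and RER are measured at t=450-480. The lipid-induced insulin resistance that the trial depends on would then be waning by an unknown amount.

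**Working it through.** **Inputs.** Carnitine: bolus 4 mg/kg over 10 min, then 4 mg/kg/h (5.1, 6.6, 8.3). Lipid: 90 ml/h of a 20% emulsion, so 0.2 g fat per ml (6.6, 8.3). Tracer start t=0, insulin t=120-480, stop after t=480 (8.3). Limits: 30 mg/kg/day carnitine and 3 g/kg fat (6.6).

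**Formula.** Total carnitine = bolus + rate × time after the bolus. Lipid volume = rate × time.

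**Step 1: reproduce the stated totals with a six-hour infusion.**
- Carnitine, 10 + 350 min: 4 + 4 × 350/60 = 27.3 mg/kg. Counting six full hours after the bolus: 4 + 4 × 6 = 28, the protocol's figure. At the rounded 0.07 mg/kg/min: 4 + 0.07 × 350 = 28.5. All are below 30.
- Lipid: 90 × 6 = 540 ml, and 540 × 0.2 = 108 g, as stated.

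The protocol's totals therefore belong to a six-hour infusion.

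**Step 2: section 8.3 as printed, t=0 to t=480.**
- Carnitine: 4 + 4 × 470/60 = 35.3 mg/kg. Excess over the limit: (35.3 − 30)/30 = 18%.
- The limit is reached at 10 + (30 − 4)/4 × 60 = 400 min, so at t=400, 50 min before the endpoint window opens.
- Lipid run to the stated stop: 90 × 8 = 720 ml = 144 g, against the stated maximum of 540 ml (108 g). It stays under 3 g/kg for anyone above 144/3 = 48 kg; at an assumed 70 kg it is 144/70 = 2.06 g/kg.
- Lipid held to six hours: it ends at t=360, and 450 − 360 = 90 min before the window.

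The two lipid readings are alternatives; only one can occur on a given day.

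**Step 3: amount already infused in the basal window with a t=0 start.**

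| | by t=90 | by t=120 |
|---|---|---|
| Lipid | 90 × 1.5 = 135 ml (27 g) | 90 × 2 = 180 ml (36 g) |
| Carnitine | 4 + 4 × 80/60 = 9.3 mg/kg | 4 + 4 × 110/60 = 11.3 mg/kg |

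**Step 4: start at t=120, stop at t=480.** Carnitine is 27.3 mg/kg and lipid 540 ml. Both infusions run through t=450-480, and nothing but tracer runs at t=90-120. Every statement in sections 3, 5.1, 6.6 and 10.8 is then met.

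**Tracer unit.** Section 8.3 gives the constant tracer rate as 0.04 ml/kg/min; section 7.6 caps it at 0.04 mg/kg/min. The prime in 8.3 is 2.4 mg/kg = 60 × 0.04 mg/kg, which fits mg. The tracer concentration is not given, so this is strong support rather than proof.

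**The case against.** The best counter-argument is that this is a label slip whose answer is already in the protocol. Section 8.3 describes insulin as running from 0 to 6 hours, so t=0 may have been meant on a second clock that starts with the clamp. On that clock, six hours of lipid gives 540 ml, and carnitine for the rest of the clamp gives 10 + 350 min. Staff dosing from section 6.6 would not give 35.3 mg/kg. The clamp SOP (appendix K6) and figure 6b are not available here and may show the right times. The safety weight is also modest: section 10.8 cites a six-hour clamp study with carnitine at 10 mg/kg/h without complications, and lipid stays under its ceiling for anyone above 48 kg.

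Much of this stands. The intended start is almost certainly t=120, the overdose is conditional on a literal reading, and no toxicity is claimed. But the second clock does not rescue the text. Section 8.3 ties the 0-to-6-hour phrase to t=120-480 in the same sentence, the only event it labels t=0 is the tracer start, and its other numbered times and appendix 2A all use the tracer clock. If figure 6b shows t=120, the text contradicts the figure. Section 8.3 is also where the protocol places these infusions on the timetable for the day, so the start time of the investigational product should not have to be inferred from other sections.

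**Conclusion.** The concern holds. The two t=0 start times in section 8.3 are wrong as written and conflict with that section's own clock and with sections 3, 5.1, 6.6 and 10.8. Taken literally, they give 35.3 mg/kg carnitine (18% over the limit of 30) and a basal RER measured after 135-180 ml lipid and, in the carnitine arm, 9.3-11.3 mg/kg carnitine. Lipid either exceeds its stated maximum by 180 ml or stops 90 minutes before the endpoint window.

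These sizes rest on the infusion rates as stated and on staff following the printed start and stop times. None of the consequences arises with a start at t=120. This must be corrected before dosing, because it is an operative dosing time that touches a stated safety limit and a main endpoint.

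**What to change.** In section 8.3:

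- Lipid or saline: 90 ml/h from t=120 to t=480.
- Carnitine or matching saline: bolus t=120-130, then 4 mg/kg/h from t=130 to t=480 (350 min).
- State the stop of both infusions as t=480, and check that figure 6b and the clamp SOP agree.
- Give the tracer rate as 0.04 mg/kg/min, to match section 7.6.

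The durations and limits in sections 5.1, 6.6 and 10.8 can stay as they are. Pump rates are best set from 4 mg/kg/h rather than the rounded 0.07 mg/kg/min.

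The cost is two start times, one stop time and one unit. No subjects, procedures or analyses are added.

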#### Muscle biopsy

In total 6 muscle biopsies will be taken during the entire study. Before and at the end of 6-hour hyperinsulinemic euglycemic clamp in all three intervention arms (saline infusion, lipid infusion, lipid infusion + carnitine) a muscle biopsy will be taken. The biopsies will be taken from the Vastus Lateralis muscle via a 5mm diameter side cutting needle after local anesthesia with Lidocaine (1.0% Lidocaine without adrenaline), according to the Bergstrom technique [16] (for a detailed description see the SOP in appendix K6). Biopsies will be taken alternately from both legs, and the first biopsy of each subjects will be randomised. So a random determination of muscle biopsy in the left or right leg will be followed (see section 8.2 and appendix 1B). Muscle tissue will be used for immunohistochemical analysis and for culturing of muscle cells, in order to be able to do full characterization of the phenotype of these muscle cells. The amount of muscle tissue needed for these analysis is about 300 mg; this is the normal size of a muscle biopsy.

### **8.4 Withdrawal of individual subjects**

Subjects can leave the study at any time for any reason if they wish to do so without any consequences. The investigator can decide to withdraw a subject from the study for urgent medical or study related reasons.

#### **8.4.1 Specific criteria for withdrawal (if applicable)**

Subjects will be withdraw from the study if the research team becomes aware of any of the following conditions:

- non medical reasons (subjects' request or non compliance with the treatment regimen)
- medical reasons considered significant by the subject and/or investigator
- protocol violation

In case of illness or use of medication the subject and/or the principal investigator with the physician will decide whether or not the subject may continue the study.

### **8.5 Replacement of individual subjects after withdrawal**

Subjects will be replaced after withdrawal

## **8.6 Follow-up of subjects withdrawn from treatment**

After withdrawal, no follow-up of the subject will take place. In case of withdrawal due to medical complications, subjects will be guided to adequate care by the responsible physician if necessary, or subjects will be referred to a general physician.

## **8.7 Premature termination of the study**

Not applicable.

# **9. SAFETY REPORTING**

## **9.1 Temporary halt for reasons of subject safety**

In accordance to section 10, subsection 4, of the WMO, the sponsor will suspend the study if there is sufficient ground that continuation of the study will jeopardise subject health or safety. The sponsor will notify the accredited METC without undue delay of a temporary halt including the reason for such an action. The study will be suspended pending a further positive decision by the accredited METC. The investigator will take care that all subjects are kept informed.

## **9.2 AEs, SAEs and SUSARs**

### **9.2.1 Adverse events (AEs)**

Adverse events are defined as any undesirable experience occurring to a subject during the study, whether or not considered related to L-carnitine (Carnitene®). All adverse events reported spontaneously by the subject or observed by the investigator or his staff will be recorded.

